## Testing the hypothesis

All adult patients (> 18 years) starting intravenous and/or oral antibiotic treatments during hospitalisation will be included in the study. Written informed consent will be obtained by every patient before study inclusion. Exclusion criteria will be pregnancy and recent nose surgery. Patients starting antibiotic therapy *per os *and/or intravenously will be sampled at antibiotic start (t_0_, within one hour) and at the following intervals: day 3 (t_1_), 7 (t_2_), 15 (t_3_), 30 (t_4_) (Figure 1). Patients colonised with MRSA and/or extended-spectrum β-lactamase (ESBL)-producing gram-negative bacteria before starting antibiotic therapy (t_0 _sample) will be excluded from follow-up cultures and analysis. Patients will be followed during the hospitalisation and afterwards for a total of 30-day from the inclusion in the study. Screening will be performed in outpatient clinics after patients' discharge from the hospital, if possible.

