### Statistical analysis

The assessable population for each target organism will include all treated patients from whom baseline screening and at least one follow-up screening will be available. The incidence of colonisation will be defined by the number of new cases of colonisation for 1,000 days of antibiotic therapy. Only patients with a negative baseline (t_0_) will be included in the longitudinal analysis. The length of exposure to antibiotic therapy for patients newly colonised by ARB will be defined by the number of days between the inclusion in the study and the date of the first positive sample. The length of exposure to antibiotic therapy for patients not colonised will be defined by the number of days between the inclusion in the study and the date of antibiotic discontinuation. The colonisation pressure will be calculated for each center and defined as the average point of prevalence for antibiotic-resistant bacteria for all days until acquisition or discharge. Time-to-event analysis (in days) between the inclusion in the study and the acquisition of colonisation will be done using Kaplan-Meier curves and Cox proportional hazard regression modeling in which the number of days until acquisition will be the dependent variable. Two nested case-control studies will be performed:

#### Case control study 1

To define the impact of antibiotics on new acquisition of MRSA and ESBL-producing *Enterobacteriaceae*, a matched case-control study will be done (ratio 1:4). The control group will be selected among patients not receiving antibiotics, admitted in the same ward on the day of the corresponding case, with negative cultures at hospital admission. Matching criteria will include: age (± 5 years), sex, and total length of hospitalisation.

#### Case control study 2

To define individual level of risk related to specific antibiotics, patients acquiring MRSA and ESBL-producing *Enterobacteriaceae *will be compared with patients not acquiring ARB after starting antibiotic therapy (ratio 1:4). Previously known risk factors or clinically relevant significant variables from the univariate analysis will be considered for inclusion in multivariate logistic regression analysis. The Hosmer and Lemeshow goodness-of-fit test will be used to assess model fit.

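### Case-control study 2 sets no time-under-screening condition on its controls, so drugs used more in long-stay patients can look risky even with no true effect

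*Protocol article*

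**What the plan says.** Study numbers here follow the Statistical analysis section; the Abstract describes the two nested studies in the other order.

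- **Control group.** Under Case control study 2, patients who acquire MRSA or ESBL-producing bacteria "will be compared with patients not acquiring ARB after starting antibiotic therapy (ratio 1:4". The stated purpose is to estimate individual risk from specific antibiotics. No matching factor and no follow-up condition on controls is given.
- **Model.** Known risk factors, or clinically relevant variables significant in univariate analysis, "will be considered for inclusion in multivariate logistic regression analysis". No time term is named.
- **Assessability.** The same section, before the nested studies are introduced, defines the assessable population as "all treated patients from whom baseline screening and at least one follow-up screening will be available".
- **Schedule.** Testing the hypothesis sets swabs at "day 3 (t_1_), 7 (t_2_), 15 (t_3_), 30 (t_4_) (Figure 1" and states that "Patients will be followed during the hospitalisation and afterwards for a total of 30-day from the inclusion in the study". It then qualifies this: "Screening will be performed in outpatient clinics after patients' discharge from the hospital, if possible". The Abstract adds a swab at discharge.
- **Contrast.** Total length of hospitalisation is a matching criterion in case-control study 1 only.
- **Variables.** The list for cases and controls contains duration of antibiotic therapy, but not length of stay, days under screening or number of swabs.

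**The concern.** Not acquiring is not one state under these rules. It can mean a single negative swab on day 3, or negative swabs through day 30, and both patients would count as the same kind of control. A patient screened for longer has more time to acquire and more occasions to be found positive. Since swabs after discharge are conditional, time under screening follows length of stay, and stay is likely to differ between users of different drugs.

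Users of long-stay drugs would then be over-represented among detected cases, and users of short-stay drugs among controls, even if every drug carried the same daily risk. The Background cites an MRSA risk raised 1.8-fold by antibiotics overall and 2-fold by cephalosporins, so an artefact of similar size could be read as a drug effect. The protocol expects its results to influence prescribing policy.

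**Working it through.** **What the plan gives.** It states no expected odds ratio, power or follow-up distribution for study 2, so there is no figure for this analysis to reproduce. The related figures are acquisition proportions of 3% (MRSA) and 5% (ESBL) in Sample size. The MRSA figure agrees with the enrolment target: 257 / 0.03 = 8567, against 8565 stated.

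**Assumptions (not in the documents).** The 5% is read as risk by day 30. The daily hazard is constant and the same for every drug, before and after discharge, so the true odds ratio is 1. Every patient has a discharge swab. A share s of discharged patients returns and is screened to day 30.

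**Formulas.**
- h = −ln(0.95)/30 = 0.00171 per day.
- Risk detected by day d: p(d) = 1 − exp(−h·d). This gives p(4) = 0.0068, p(20) = 0.0336, p(30) = 0.0500.
- Proportion detected with discharge on day d: s·p(30) + (1 − s)·p(d).
- Drawing controls 1:4 without regard to drug leaves the expected odds ratio unchanged.

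**No overlap.** All users of one drug leave on day 4, all users of the other on day 20. At s = 0.2:
- short stay: 0.2 × 0.0500 + 0.8 × 0.0068 = 0.0155
- long stay: 0.2 × 0.0500 + 0.8 × 0.0336 = 0.0369
- odds ratio: (0.0369/0.9631) / (0.0155/0.9845) = 2.4

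**Overlap.** 70% of one drug's users and 30% of the other's are long-stay. At s = 0.2:
- first drug: 0.7 × 0.0369 + 0.3 × 0.0155 = 0.0305
- second drug: 0.3 × 0.0369 + 0.7 × 0.0155 = 0.0219
- odds ratio: 1.4

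**Null odds ratio by share returning.**

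| Discharge days | Overlap in stay | 0% | 20% | 40% | 60% | 100% |
|---|---|---|---|---|---|---|
| 4 v 20 | none | 5.1 | 2.4 | 1.7 | 1.3 | 1.0 |
| 4 v 20 | 70/30 v 30/70 | 1.7 | 1.4 | 1.2 | 1.1 | 1.0 |
| 7 v 15 | none | 2.2 | 1.6 | 1.3 | 1.2 | 1.0 |
| 7 v 15 | 70/30 v 30/70 | 1.3 | 1.2 | 1.1 | 1.1 | 1.0 |

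**Check of the remedy.** 500 cohorts of 8565 were simulated with a null drug used by 30%. Last swab was assumed on day 3/7/15/30 in 10/30/40/20% of its users and 40/40/15/5% of the others, with no further returns. Controls drawn from all non-acquirers gave an average odds ratio of 1.90. Controls drawn from patients still screened and negative at the case's swab day, analysed in strata of that day, gave 1.00.

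**The case against.** **The article may simply be short.** Study 2 gets a few sentences, and nested case-control studies are often sampled from risk sets. The full protocol may do this. It stands that the article does not rule out such sampling. But it does fix a comparison group, a ratio and a model for study 2, and it states matching on stay for study 1 alone. Followed as written, the plan allows the bias.

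**The one-swab rule is not stated for study 2.** Correct. It opens the cohort analysis, and applying it to study 2 is an inference from the study being nested in that cohort.

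**The covariate list is open.** Also correct: length of stay could enter as a known risk factor. The supportable statement is that no time variable is named. Total stay is in any case not the same as time under screening up to the case's swab.

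**Other analyses handle time.** The primary rate per 1,000 antibiotic-days is also reported by class and drug, and a Cox model is planned. They account for time and give a comparison, but they do not correct study 2's odds ratios.

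**The stronger reading.** A reader might infer that long-stay drugs will look risky only because their users are swabbed for longer, by a factor of about 5. The documents do not support that. They give neither the link between drug and stay nor the return rate, and the factor of 5 needs complete separation of stays and no returns.

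**Acquisition may be mainly in hospital.** The Background concerns nosocomial carriage. If all acquisition stopped at discharge, complete day-30 swabs would not help: the table's 0% column would apply at every return rate, and the distortion would be time in hospital rather than missed detection. This stands and limits what control sampling alone can repair.

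**Conclusion.** The concern holds in a limited form. As written, study 2 can produce raised odds ratios for drugs used more in long-stay patients when there is no true effect, because nothing stated for it equalises time under screening.

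The size is not known. For discharge on day 4 versus day 20, 5.1 falling to 1.3 (0 to 60% return) is an upper bound that assumes no overlap in stay. With a 70/30 versus 30/70 mix the range is 1.7 to 1.1. Under a constant hazard the bias disappears if everyone has a day-30 swab. These figures rest on the assumed discharge days, return rates and hazard, and on the assessability rule reaching study 2. The primary rate and the Cox analysis are outside this point. It deserves correction before study 2 is analysed, because the remedy is cheap.

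**What to change.** Add to Case control study 2:

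1. Draw each case's four controls by incidence-density sampling from treated patients still under screening, with a negative swab at or after the scheduled visit at which the case was first positive. Do not accept a patient whose last swab was earlier.
2. Analyse with conditional logistic regression, or stratify on that visit. The sampling rule should not be paired with an ordinary logistic model that ignores the time matching.
3. Consider length of stay up to that day as a covariate. A patient discharged on day 4 with a negative day-30 swab remains an eligible control, so sampling alone does not equalise time in hospital.
4. Report the day of last swab for cases and controls, so that readers can judge any remaining imbalance.

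The cost is a few sentences in the plan. Swab dates are needed for the planned time-to-event analysis anyway, so no new visits or samples are required. The downside is fewer eligible controls for cases first positive at t3 or t4, where fewer patients remain under screening.

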### Sample size

Since the rate of acquisition of ESBL-producing gram-negative bacteria in patients receiving antibiotic therapy has not been established in prospective cohort studies, prevalence proportion was derived from retrospective case-control studies and defined as 5%. Sample size calculation for the rate of new acquisition of MRSA has been derived by a previous study where the acquisition rate, after starting antibiotic therapy, was 3% [4]. To be able to analyse 257 patients newly colonised by MRSA and 443 by ESBL-producing gram-negative, 8565 patients starting antibiotic therapy need to be enrolled. According to the number of hospital admission/year and percentage of patients starting antibiotic in each ward, the clinical centers are required to provide the following numbers of patients with new colonisation by MRSA/ESBL *Enterobacteriaceae*: 48/95, 121/201, and 88/147 for UCSC, IDMB, CCS, respectively.

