## Background

Despite many efforts, the control of nosocomial antibiotic-resistant infections is still a permanent and unresolved issue in healthcare institutions worldwide facing increased morbidity, mortality and hospital costs [1-3]. Selective pressure exerted by antibiotics plays a central role on the acquisition, selection, persistence and transmission of resistant pathogens which may include the following effects: (1) eradication of the susceptible skin and gut flora will increase the likelihood of acquisition of antibiotic-resistant organisms, especially in settings with endemic resistance; (2) antibiotics select for pre-existing antibiotic-resistant bacteria (ARB) in carriers and enhance the likelihood of spread; (3) antibiotic selection pressure may transform low-level carriers to high-level spreaders; (4) antibiotics active against antibiotic-susceptible bacteria may convert carriers of susceptible bacteria to non-carriers, indirectly promoting acquisition and spread of ARB; (5) antibiotic exposure may increase the risk of endogenous infection with ARB related to changes in colonisation resistance and bacterial virulence at the individual host level [4]. Numerous papers demonstrated that prior antimicrobial drug exposure is a strong risk factor for colonisation and infection due to a drug resistant pathogen [5,6]. A meta-analysis that included 76 studies for a total of 24,230 patients documented that the risk of acquiring methicillin-resistant *Staphylococcus aureus *(MRSA) was increased by 1.8-fold in patients who had taken antibiotics. Antibiotic exposure was determined in the 126 days preceding MRSA isolation [7]. Such risk was almost 3-fold greater after using quinolones or glycopeptides and 2-fold for cephalosporins. A multicentre prospective cohort study conducted in several Italian hospitals showed that 5% of patients were newly colonised by ARB including MRSA in nasal samples, after starting antibiotic therapy. Nine percent of those patients developed an infection by the same strain over the 30-day follow-up. The use of carbapenems was associated with the highest incidence of colonisation with eight new cases of MRSA colonisation for 1,000 antibiotic-day [4].

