The likelihood of acquisition of nosocomial ARB during or shortly after therapy with different antibiotic agents is still unclear and is often confounded by scarce data on antibiotic usage at the individual patient level. Study design, selection bias, definition of control groups and failure to control for confounding variables might account for conflicting results [8]. No prospective multi-centre cohort study has been conducted defining, in countries with varying baseline antimicrobial resistance rates, the impact of antibiotic exposure on the development and acquisition of nosocomial carriage by ARB, after accounting for individual and group-level confounding variables, such as case-mix and colonisation pressure [8-10].

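### The target of 443 ESBL acquisitions rests on a case-control prevalence, and 5% of 8,565 gives 428, not 443

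*Protocol article*

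**What the plan says.** The Sample size section of the protocol article uses two planning rates of different kinds.

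- **ESBL.** The acquisition rate under antibiotic therapy "has not been established in prospective cohort studies", so a "prevalence proportion was derived from retrospective case-control studies and defined as 5" per cent.
- **MRSA.** The rate was "derived by a previous study where the acquisition rate, after starting antibiotic therapy, was 3" per cent. The source is the study cited as [4], which the Background describes as a multicentre prospective cohort.

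The target follows: "To be able to analyse 257 patients newly colonised by MRSA and 443 by ESBL-producing gram-negative", "8565 patients starting antibiotic therapy need to be enrolled". The section then says that "the clinical centers are required to provide the following numbers of patients with new colonisation by" MRSA/ESBL: 48/95 at UCSC, 121/201 at IDMB and 88/147 at CCS.

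Elsewhere, Outcomes defines the primary outcome as acquisition per 1,000 antibiotic-days. Testing the hypothesis removes patients who carry either organism at t0. Statistical analysis keeps only t0-negative patients in the longitudinal analysis, and requires a baseline and at least one follow-up screen for the assessable population.

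**The concern.** A prevalence counts people who already carry the organism. Those are the patients this study takes out at t0. What has to be planned is the proportion of t0-negative patients who acquire ESBL carriage during follow-up, and the two proportions need not be close.

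The source adds a second difficulty. A case-control study sets the ratio of cases to controls by design, so the share of cases in it says nothing about how common the condition is, unless sampling fractions or the size of the underlying cohort are known. The article mentions neither.

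The figure is then used as if it were firm: a single case count, no range, and centre requirements expressed as numbers of outcomes. A centre can undertake to enrol patients, but it cannot undertake to supply acquisitions. The number of ESBL cases governs the precision of the ESBL results by antibiotic class and drug, so the stated count should at least follow from the stated inputs.

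**Working it through.** **Inputs** (all from Sample size): N = 8,565; MRSA rate 3%; ESBL rate 5%; targets 257 and 443; the centre figures above. The article gives no attrition allowance and no power statement, so none is used.

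**1. Reproduce the plan's totals.** Expected cases = N × rate; required N = cases / rate.

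- MRSA: 8,565 × 0.03 = 256.95, stated 257. In reverse, 257 / 0.03 = 8,567, stated 8,565. Both agree to rounding.
- ESBL: 8,565 × 0.05 = 428.25, stated 443, a difference of 14.75. In reverse, 443 / 0.05 = 8,860, which is 295 more than 8,565. The stated pair implies 443 / 8,565 = 5.17%.
- The centre figures add up: 48 + 121 + 88 = 257 and 95 + 201 + 147 = 443.

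**2. Locate the difference.** Patients per centre = MRSA cases / 0.03; ESBL cases expected at 5% of that number.

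| Centre | MRSA stated | Implied patients | ESBL at 5% | ESBL stated | Implied ESBL rate |
|---|---|---|---|---|---|
| UCSC | 48 | 1,600 | 80 | 95 | 5.94% |
| IDMB | 121 | 4,033 | 202 | 201 | 4.98% |
| CCS | 88 | 2,933 | 147 | 147 | 5.01% |

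IDMB and CCS reproduce to within one case. The excess is at UCSC: 95 − 80 = 15.

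**3. Possible explanations for 443.**

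- *A rounded rate (5.17% shown as 5%).* This would give 4,033 × 0.0517 = 209 at IDMB and 2,933 × 0.0517 = 152 at CCS, against 201 and 147. It does not fit.
- *Inflation for the 3% who acquire MRSA.* 428.25 / 0.97 = 441.5. This is near 443, but no such step is stated and the MRSA total reproduces without one.
- *More patients at UCSC.* 95 / 0.05 = 1,900, which contradicts the 1,600 implied by its MRSA figure.

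**4. Who is in the denominator.** Both 257 and 428 apply the rate to everyone enrolled. If a fraction f is t0-positive or has no follow-up swab, expected cases are 8,565 × (1 − f) × rate. The article gives no value for f; as assumptions only:

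- f = 5%: 244 MRSA, 407 ESBL
- f = 10%: 231 MRSA, 385 ESBL
- f = 20%: 206 MRSA, 343 ESBL

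**5. Sensitivity to the ESBL rate.** The documents give no ESBL acquisition proportion, so this range is an assumption in both directions. The standard error of a log odds ratio is taken as proportional to 1/√cases at a fixed control ratio and the same exposure pattern.

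| Assumed rate | Cases from 8,565 | Patients needed for 443 | SE relative to 443 cases |
|---|---|---|---|
| 2% | 171 | 22,150 | √(443/171.3) = 1.61 |
| 5% | 428 | 8,860 | √(443/428.25) = 1.02 |
| 8% | 685 | 5,538 | √(443/685.2) = 0.80 |

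**The case against.** The best defence is that the article is open about the weakness. It says that no prospective ESBL rate was available and that 5% was a defined value. The source studies are not shown, and a case-control study nested in a known cohort can report a denominator. That stands as far as it goes: the 5% is a disclosed planning assumption, and it cannot be said that no denominator existed. But even a sound prevalence is not an acquisition proportion, and disclosure does not explain why 5% of 8,565 should be 443.

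It is also fair to say that the consequence is limited. The study is an observational cohort, the article makes no power claim, and final precision will depend on the cases that accrue.

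A reader might infer four stronger things, which the documents do not support:

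- *That the whole sample size is unfounded.* The 8,565 and the MRSA figures of 48/121/88 reproduce from the separate 3% acquisition rate. The IDMB and CCS ESBL figures follow arithmetically from 5%.
- *That one 5:3 ratio was imposed on all centres despite known differences.* The ratios are 201/121 = 1.66 and 147/88 = 1.67, but 95/48 = 1.98 at UCSC. The Background phrase "in countries with varying baseline antimicrobial resistance rates" belongs to a sentence about a gap in earlier research and gives no rates for these centres.
- *That centres will enrol until they reach their case numbers, which would distort the pooled rate.* No such rule is stated. The enrolment total is fixed, and the split is attributed to admissions and antibiotic use per ward, so the requirement can be read as expected yield.
- *That ESBL cases will fall well short because the true rate is nearer 2%.* Nothing in the documents supports 2% over 8%. The direction of error in the 5% is unknown.

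**Conclusion.** The point holds in a limited form. The ESBL planning rate is described as a prevalence from a design that does not by itself yield one, and it is used for new acquisition in patients from whom carriers have been removed. Separately, the stated ESBL count is not what the plan's own inputs deliver: 428 rather than 443, a shortfall of about 15 cases or 3.3% of the target, arising at UCSC.

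The arithmetic gap alone is small, with standard errors about 2% larger. The larger uncertainty is the 5% itself and the absence of any visible allowance for t0-positive or unassessable patients. The size of neither can be fixed from the documents. The centre check assumes that 3% was applied at every centre, which fits the overall MRSA total and the ESBL figures of two of the three centres. If the authors used a different UCSC rate or volume, the 95 may have a reason, but it is not given. Enrolment of 8,565 does not depend on the 5% and need not change.

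**What to change.** Amend the Sample size section as follows.

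1. Describe 5% as an assumed proportion of t0-negative patients newly acquiring ESBL carriage, and drop the term prevalence.
2. Restate expected ESBL cases as about 428, with UCSC about 80, or explain how 443 and 95 were obtained.
3. Say that these counts, like the 257 for MRSA, are before removal of t0-positive patients and those without a follow-up swab, or add an explicit allowance.
4. Give a two-sided range, for example 171 cases at 2% to 685 at 8%, labelled as an assumption.
5. State centre requirements as patients starting antibiotics to be enrolled, about 1,600 / 4,033 / 2,933 for UCSC / IDMB / CCS by the plan's own 3%, with case numbers as expectations.

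The cost is rewording. The stated ESBL case number becomes slightly less favourable. No patients are added and no analysis changes.

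### The ESBL target of 443 does not follow from 8,565 patients at 5%, which gives 428; the excess of 15 lies in one centre's target (95 at UCSC, where the stated rates give 80)

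*Protocol article*

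**What the plan says.** Everything needed is in the Sample size section of the protocol article.

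- **ESBL rate.** In the absence of prospective data, the "prevalence proportion was derived from retrospective case-control studies and defined as 5" per cent.
- **MRSA rate.** In an earlier study "the acquisition rate, after starting antibiotic therapy, was 3" per cent.
- **Case targets and enrolment.** To analyse "257 patients newly colonised by MRSA and 443 by ESBL-producing gram-negative, 8565 patients starting antibiotic therapy" must be enrolled. The enrolment is one number for both organisms.
- **Centre targets (MRSA/ESBL).** "48/95, 121/201, and 88/147 for UCSC, IDMB, CCS, respectively".
- **Basis of the centre targets.** "According to the number of hospital admission/year and percentage of patients starting antibiotic in each ward". This describes patient volume only.

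The section gives no centre-specific acquisition rate, no allowance for dropout and no other inflation factor.

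**The concern.** Both organisms are sought in the same enrolled patients, so each case target should be the enrolment times the assumed proportion. The MRSA target obeys that rule and the ESBL target does not. Within a centre, a shared denominator also means that the ESBL target should be 5/3 = 1.67 times the MRSA target. Patient volume scales both targets alike and cannot change that ratio. One of the three centres breaks it.

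At stake is whether the plan's case numbers can be relied on. The ESBL acquirers are the cases for two nested case-control studies at 1:4 (Statistical analysis section). An overstatement of 15 cases is therefore also an overstatement of 15 × 4 = 60 controls in each study for that organism. A centre monitored against 95 ESBL cases would look deficient even if its enrolment and acquisition rate were exactly as the other stated figures imply.

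**Working it through.** **Inputs**, all from the Sample size section: N = 8,565; p(MRSA) = 0.03; p(ESBL) = 0.05; totals 257 and 443; centre targets 48/95 (UCSC), 121/201 (IDMB) and 88/147 (CCS).

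**1. Reproduce the plan's MRSA figure.** Expected cases = N × p = 8,565 × 0.03 = 256.95, which rounds to the stated 257. This confirms the rule that was used.

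**2. Apply the same rule to ESBL.** 8,565 × 0.05 = 428.25, against 443 stated. The difference is 14.75, and 14.75 / 428.25 = 3.4%. In reverse, 443 / 0.05 = 8,860 patients, and 8,860 − 8,565 = 295.

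**3. Check the addition.** 48 + 121 + 88 = 257 and 95 + 201 + 147 = 443. The totals agree with the centre targets, so the problem is not a summing error.

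**4. Check each centre.** Implied patients = MRSA target / 0.03; implied ESBL cases = implied patients × 0.05.

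| Centre | Patients implied by MRSA | ESBL implied | ESBL stated | Difference | ESBL/MRSA as stated |
|---|---|---|---|---|---|
| UCSC | 48 / 0.03 = 1,600 | 80.0 | 95 | +15.0 | 1.98 |
| IDMB | 121 / 0.03 = 4,033 | 201.7 | 201 | −0.7 | 1.66 |
| CCS | 88 / 0.03 = 2,933 | 146.7 | 147 | +0.3 | 1.67 |

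The implied sizes add to 257 / 0.03 = 8,567, in line with 8,565.

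**5. Allow for rounding of the targets** by ±0.5 case.

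- IDMB: sizes from 4,017 to 4,030 satisfy both of its targets.
- CCS: sizes from 2,930 to 2,950 satisfy both.
- UCSC: 48 needs 1,583 to 1,617 patients (47.5/0.03 to 48.5/0.03), while 95 needs 1,890 to 1,910 (94.5/0.05 to 95.5/0.05). The ranges do not meet.

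**6. Size UCSC without using its own targets.** Subtracting the other two centres from the enrolment leaves between 8,565 − 4,030 − 2,950 = 1,585 and 8,565 − 4,017 − 2,930 = 1,618 patients. At 5% that is 79 to 81 ESBL cases, which fits 80 and not 95.

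**7. Substitute 80 for 95.** 80 + 201 + 147 = 428, which is the N × 5% result.

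**8. Try other explanations.** A dropout inflation N/(1 − d) would need d = 1 − 428.25/443 = 3.3%, which is not stated. Leaving MRSA acquirers out of the ESBL denominator gives (8,565 − 257) × 0.05 = 415. Treating 5% as a cumulative risk and converting it to a rate gives −ln(0.95) × 8,565 = 439. None gives 443, apart from the dropout figure chosen to do so, and any general adjustment would move all three centres rather than one.

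**The case against.** The arithmetic itself is hard to dispute. The best opposing points concern what may be inferred from it.

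- **428 is an expectation, not a ceiling.** With N = 8,565 and p = 0.05 the binomial standard deviation is √(8,565 × 0.05 × 0.95) ≈ 20, so the gap is about 0.7 standard deviations. If patients are independent, 443 or more cases would occur about one time in four. This stands: 443 is attainable by chance, but it is not the number that the stated assumptions lead one to expect.
- **443 / 8,565 = 5.17%, which rounds to 5%.** This is fair for the total alone. It does not help at UCSC, where 95 / 1,600 = 5.9%.
- **The UCSC size of 1,600 is inferred.** The article gives no enrolment by centre, and 95 / 0.05 = 1,900 is the other reading. But the residual from the other two centres (step 6) supports about 1,600 independently of UCSC's own targets.
- **Rates or denominators may differ.** The Background speaks of countries with varying baseline resistance, and the Statistical analysis section defines an assessable population for each organism. Neither supplies a figure that yields 95. The Sample size section gives one ESBL proportion and one enrolment, and the other two centres fit them.
- **The effect is minor.** No power or precision statement depends on 443. Going from 443 to 428 cases widens a standard error by about 1.7% (√(443/428) = 1.017). This also stands, and it limits the weight of the point without removing it.

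**Conclusion.** The concern holds. Under the stated 5%, 8,565 patients are expected to yield 428 ESBL acquisitions, not 443. The excess of 15 lies wholly in the UCSC target, which is 95 where the stated rates give 80 (15/80 = 19% too high). The conclusion assumes that the 3% and 5% apply at every centre and that both organisms share one denominator per centre. The section states single rates and one enrolment, and IDMB and CCS agree with that reading to within rounding.

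The document does not prove which figure slipped: the 95 (and with it 443), the uniform 5%, or the enrolment. The 95 is the likeliest, because changing it and the total that contains it brings every other figure into agreement. The consequence is modest. The validity of the planned analyses is not affected, but the ESBL target and one centre's required contribution are not what the plan's own assumptions deliver.

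**What to change.** Check the source calculation for UCSC and make the section consistent in one of these ways:

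1. **Preferred, if 95 is a slip:** state the ESBL total as 428 and the UCSC target as 48/80, keeping 8,565 and the other figures. This costs one corrected total and one corrected site target; the stated number of ESBL cases falls by 15.
2. **If a higher ESBL rate was intended at UCSC:** state that rate (95 / 1,600 = 5.9%) with its basis, and say that 5% applies only to the other two centres. The cost is one added sentence, and 443 stays.
3. **If 443 at a uniform 5% is really required:** raise enrolment to 8,860, with UCSC at about 1,900 patients. Its MRSA target becomes 1,900 × 0.03 = 57 and the MRSA total 57 + 121 + 88 = 266. This means enrolling 295 more patients and is the only costly option.

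In each case, give the planned enrolment by centre so that the targets can be checked.

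### The 8,565 to be enrolled yields 257 MRSA cases only if every enrolled patient is analysable, and at 5% it yields 428 ESBL cases, not the stated 443

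*Protocol article*

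**What the plan says.** The Sample size section of the protocol article assumes an acquisition proportion of 3% for MRSA, taken from an earlier study. For ESBL producers it assumes 5%, taken from retrospective case-control studies. It then links cases to enrolment: "To be able to analyse 257 patients newly colonised by MRSA and 443 by ESBL-producing gram-negative", it says, "8565 patients starting antibiotic therapy need to be enrolled". The MRSA/ESBL case numbers required of the centres are "48/95, 121/201, and 88/147 for UCSC, IDMB, CCS, respectively". No allowance for loss is stated.

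Two other sections define who is analysed:

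- Testing the hypothesis includes all adults who start oral or intravenous antibiotics in hospital. Those found colonised with MRSA and/or ESBL producers at t0 "will be excluded from follow-up cultures and analysis". Outpatient screening is to follow "discharge from the hospital, if possible".
- Statistical analysis limits the assessable population for each organism to "all treated patients from whom baseline screening and at least one follow-up screening will be available", and the longitudinal analysis to patients negative at t0.

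**The concern.** The sample size statement treats patients enrolled and patients analysed as the same number, while the rest of the article makes the second smaller than the first. Carriers at t0 are enrolled before their result is known and then leave. Patients without any follow-up screening leave as well. The case numbers also ought to follow from the stated rates, and one of them does not.

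The case counts are the only stated basis for the study's size, and they are passed on to the three centres as requirements. The cases feed both nested case-control studies and the rates by antibiotic class and single drug. A reader who takes 257 and 443 as what 8,565 enrolled patients will deliver may be planning on more cases than the design supplies.

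**Working it through.** **Inputs from the Sample size section.** MRSA 3%; ESBL 5%; cases 257 and 443; enrolment 8,565; centre targets (MRSA/ESBL) UCSC 48/95, IDMB 121/201, CCS 88/147. No alpha, power or effect size is given, so the only formulas that apply are expected cases = N × p and N = cases / p.

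**Step 1: reproduce the plan's figures with no loss.**

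- MRSA: 8,565 × 0.03 = 256.95, and 257 / 0.03 = 8,566.7. This reproduces.
- ESBL: 8,565 × 0.05 = 428.25, and 443 / 0.05 = 8,860. This does not reproduce. The gap is 443 − 428 = 15 cases. Reaching 443 from 8,565 needs a rate of 443 / 8,565 = 5.17%.

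**Step 2: locate the gap.** The centre targets add up: 48 + 121 + 88 = 257 and 95 + 201 + 147 = 443. Dividing each target by its rate gives the implied number of patients:

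| Centre | MRSA / 0.03 | ESBL / 0.05 | ESBL expected at 5% of the MRSA-implied number | ESBL target |
|---|---|---|---|---|
| UCSC | 1,600 | 1,900 | 80 | 95 |
| IDMB | 4,033 | 4,020 | 201.7 | 201 |
| CCS | 2,933 | 2,940 | 146.7 | 147 |

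IDMB and CCS agree to within rounding. The whole excess is at UCSC: 95 − 80 = 15. With 80 in place of 95, the ESBL targets sum to 80 + 201 + 147 = 428, which is 5% of 8,565.

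**Step 3: effect of the exclusions.** Let c be the proportion excluded as carriers at t0 and d the proportion of the remainder with no follow-up screening. Analysable patients = 8,565 × (1 − c) × (1 − d). The documents give neither c nor d, so the values below are assumptions. The 3% and 5% are taken as rates per analysable patient.

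| c | d | Analysable | MRSA cases | ESBL cases |
|---|---|---|---|---|
| 0 | 0 | 8,565 | 256.9 | 428.2 |
| 5% | 5% | 7,730 | 231.9 | 386.5 |
| 10% | 10% | 6,938 | 208.1 | 346.9 |
| 10% | 20% | 6,167 | 185.0 | 308.3 |
| 20% | 20% | 5,482 | 164.4 | 274.1 |

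At 10% and 20%, the MRSA count is 1 − 185/257 = 28% below target. The ESBL count is 1 − 308/443 = 30% below target; 15 of those 135 missing cases come from step 1 and not from exclusions.

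**Step 4: chance of reaching the targets.** Treating patients as independent (binomial), the chance of at least 257 MRSA cases is 51% with no loss and about 5% with 10% total loss (7,708 analysable). The chance of at least 443 ESBL cases is 24% with no loss and about 0.2% with 10% total loss.

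**The case against.** The strongest counter-argument concerns the denominator. If the source rates were counted over all treated patients, carriers and patients without follow-up included, they already absorb some or all of the loss, and 3% of everyone enrolled is the right calculation. The article does not say which denominator applies. This stands, and it makes the MRSA shortfall conditional. It does not rescue 443, which differs from 5% of 8,565 under either reading.

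The size of the loss is also unknown. A reader might infer heavy loss from the conditional wording on outpatient swabs. But a patient needs only one follow-up screening, the first is due on day 3, and the Abstract also plans screening at discharge. Missing late outpatient swabs do not by themselves make a patient unassessable. Using one carriage figure for both organisms is a simplification too: Testing the hypothesis excludes carriers of either organism, whereas the assessable population is defined per organism.

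The centre figures are worded as requirements, so recruitment might in practice run until they are met, and UCSC might expect a higher ESBL rate (95 / 1,600 = 5.94%). The article states neither. In the first case 8,565 would not be the number needed; in the second a uniform 5% would not be the assumption.

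Finally, this is a condensed article, and a fuller protocol may hold an attrition allowance. That would excuse silence. It does not reconcile figures that the article itself states and that do not agree.

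**Conclusion.** The concern holds in limited form. Two statements need nothing from outside the article: 257 is 3% of all 8,565 enrolled, with nothing set aside for exclusions the plan itself prescribes; and 443 is not 5% of 8,565 but exceeds it by 15 cases, all in the UCSC target. A third is conditional: if the rates are per analysable patient, any loss puts the expected MRSA count below 257, and the expected ESBL count falls further below 443.

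Three stronger conclusions that a reader might draw are not supported:

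- That the targets will not be reached. This depends on the unstated denominators and on carriage and loss figures that are assumed here.
- That precision for single-drug rates is overstated. The article states no precision.
- That the 5% is invalid because of its case-control origin. The article says that no prospective rate was available and presents 5% as a planning assumption; how the sources were used cannot be seen.

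**What to change.** Keep 8,565 as the number enrolled and amend the Sample size section as follows:

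1. State whether the 3% and 5% are per treated patient or per t0-negative patient with at least one follow-up screening.
2. Reconcile 443 and the UCSC target of 95 with the 5%, by correcting them (428 and 80 before exclusions) or by stating the rate that produces them.
3. If the rates are per analysable patient, restate the expected MRSA and ESBL cases and the centre targets after exclusions. Implications of the hypothesis says recruitment is under way at all centres, so the proportions observed so far as t0-positive and without follow-up can replace the assumed values.

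The cost is a few restated figures, with less favourable case numbers. No extra patients are required. Relabelling 8,565 as the number of assessable patients is not proposed, because it would raise enrolment: at 10% carriage and 20% loss, to about 8,565 / 0.72 = 11,896.
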